## Abstract

**Background:**

Venous thromboembolism is common in patients with cancer and requires anticoagulation with low molecular weight heparin. Current data informs anticoagulation as far as six months, yet guidelines recommend anticoagulation beyond six months in patients who have locally advanced or metastatic cancer. This recommendation, based on expert consensus, has not been evaluated in a clinical study. ALICAT (Anticoagulation Length in Cancer Associated Thrombosis) is a feasibility study to identify the most clinically and cost effective length of anticoagulation with low molecular weight heparin in the treatment of cancer associated thrombosis.

**Methods/Design:**

ALICAT is a randomized multi-centre phase two mixed-methods study with three components: a randomized controlled trial, embedded qualitative study and a survey investigating pathways of care. The randomized controlled trial will compare ongoing low molecular weight heparin treatment for cancer-associated thrombosis versus cessation of low molecular weight heparin at six months treatment (current licensed practice) in patients with locally advanced or metastatic cancer. The embedded qualitative study will include focus groups with clinicians to investigate attitudes to recruiting to the study, identify the challenges of progressing to a full randomized controlled trial, and also semi-structured interviews with patients and relatives/carers to explore their attitudes towards participating in the study and potential barriers and concerns to participation. Finally, a UK wide survey exercise will be undertaken to develop a classification and enumeration system for the cancer associated thrombosis models and pathways of care.

**Discussion:**

There is a lack of evidence determining the length of anticoagulation for patients with cancer associated thrombosis and subsequently treatment length varies. The ALICAT study will consider the feasibility of recruiting patients to a phase three trial.

**Trial registration:**

Current Controlled Trials ISRCTN37913976.

## Background

Venous thromboembolism (VTE), comprising of deep vein thrombosis (DVT) and pulmonary embolus (PE), is a common phenomenon which occurs in 1 in 1,000 patients and annually affects 6.5 million people worldwide [1,2]. Within the UK, the cost of managing VTE has been estimated at £640 million per year, and the prevention of VTE has become a health service priority [3]. Individuals with cancer are at particular risk of VTE due to the local release of procoagulants, such as tissue factor, and the prothrombotic nature of oncological treatments including surgery, chemotherapy and radiotherapy [4]. Up to 18% of patients with cancer will develop VTE, requiring anticoagulation [4]. The standard treatment of VTE is well established, consisting of five days anticoagulation with low molecular weight heparin (LMWH), followed by three to six months warfarin [4,5]. However, the management of cancer associated thrombosis (CAT) presents several challenges due to a higher rate of both re-thrombosis and bleeding amongst patients with cancer when compared to those with a non-malignant disease [6].

The impact of VTE on patients with cancer is substantial; conferring a worse prognosis when compared with similar stage cancer patients without VTE [7,8]. Furthermore, anticoagulation with warfarin is complicated by drug-drug interactions, variable drug absorption, and changing nutritional status [9]. This inevitably has a practical impact on the delivery of anti-cancer therapies. Maintaining stable coagulation with warfarin is difficult and requires more frequent monitoring with blood tests, which adversely affects patients’ quality of life [10]. Three randomized controlled trials (RCTs) have compared LMWH with warfarin in the treatment of CAT, demonstrating superior efficacy with LMWH without statistical difference in bleeding complications [11-13]. Consequently, national and international clinical guidelines recommend the gold standard treatment of CAT to be six months treatment with weight adjusted LMWH [6,14-16].

The management of CAT beyond six months is less clear; in patients with locally advanced or metastatic cancer there is an ongoing prothrombotic state which may warrant anticoagulation beyond the recommended period. In support of indefinite anticoagulation are data suggesting the prothrombotic risk increases with disease progression, due to a greater tumor burden, reduced performance status and increased use of palliative chemotherapy [17-19]. However, with cancer progression also comes an increased bleeding risk during anticoagulation, and the decision to anticoagulate indefinitely will need to balance the benefits of preventing recurrent VTE against the risks of major bleeding [20,21]. Furthermore, it is important to consider the impact of long term LMWH use on patients’ quality of life.

Currently, clinical guidelines recommend clinicians consider continuing anticoagulation indefinitely in patients with locally advanced or metastatic cancer [15,16,22]. Such recommendations are based largely on consensus opinion and, to date, have been supported by limited clinical evidence beyond case series and observational studies [23,24]. In the recently reported DALTECAN (Dalteparin sodium for the long-term management of venous thromboembolism in cancer patients) study, 334 patients with VTE and locally advanced or metastatic cancer were treated with dalteparin, of whom 185 (55.4%) completed six months of therapy and 109 (33%) completed twelve months [24]. The authors reported a 10.2% overall frequency of major bleeding and an overall incidence of new or recurrent VTE of 11.1%. In patients treated during the extended anticoagulation period, new or recurrent VTE was reported in 4.1% of patients and major bleeding at a rate of 4.2%. It is notable that both bleeding and recurrent thrombosis rates were higher in the first six months of anticoagulation (1.3% and 1.4% per patient-month respectively) compared with months seven to twelve (0.7% and 0.7% per patient-month respectively) [24]. In the absence of a control arm in which patients received placebo/ceased anticoagulation at six months, the study offers no further guidance as to whether anticoagulation beyond six months provides any net benefit. However, it offers valuable data, which can be used to inform future clinical studies. Firstly, with 96% trial adherence, it suggests that the use of LMWH beyond six months is feasible within the trial setting. Secondly, it suggests that safety concerns regarding bleeding in this patient group may be less of an issue than previously believed. Furthermore, with the rate of VTE recurrence being lower during the extended anticoagulation period than the initial six months, it would seem reasonable to question what degree of added clinical benefit is gained through extended treatment, rather than ceasing anticoagulation at six months [24]. Finally, the trial did not formally evaluate quality of life aspects of LMWH administration over an extended time period.

Several clinical studies are currently attempting to clarify CAT management beyond six months anticoagulation. In the LONGHEVA (Long-term Treatment for Cancer Patients With Deep Venous Thrombosis or Pulmonary Embolism) [25] study patients who have completed six to twelve months of treatment for VTE and still have an indication for further anticoagulation (metastatic cancer and/or ongoing cancer treatment) will be randomized to receive a further six months of vitamin K antagonist (VKA) or LMWH. The primary efficacy outcome is recurrence of confirmed symptomatic DVT with secondary outcomes including safety. Driven by the belief that patients with metastatic cancer or receiving cancer treatment require extended anticoagulation, the investigators seek to establish the most efficacious anticoagulant between VKAs and LMWHs [25]. Whilst the driving hypothesis feels intuitively sensible, this belief is yet to be quantified within the trial setting. Without robust data identifying the VTE risk of *not* continuing anticoagulation it becomes conceptually challenging to justify a therapeutic intervention that is yet to be proven beneficial.

SELECT-D (Anticoagulation therapy in SELECTeD cancer patients at risk of recurrence of venous thromboembolism.) is a pilot study comparing dalteparin versus rivoraxaban in the treatment of CAT with a second placebo-controlled randomization comparing the duration of anticoagulation therapy (six months versus twelve months treatment) in residual vein thrombosis [RVT] positive patients [26]. It is wholly appropriate that this study is piloted before proceeding to a full RCT since several key factors within the study design will need clarification in advance. Firstly, the investigators have chosen to compare dalteparin with rivaroxaban, a drug that is yet to demonstrate non-inferiority in the CAT setting. Secondly, the utility of RVT as a predictor of VTE recurrence specifically in the cancer-associated thrombosis setting is yet to be established [27,28].

It is arguable that when considering anticoagulation beyond six months, one should quantify the clinical need for prolonged anticoagulation before evaluating the most appropriate drug. Scientifically, such an approach has merit since it informs future studies from a basis of fact and not supposition. However, clinical practice has developed in such a way that many clinicians will continue anticoagulation regardless of the evidence deficit. For this reason, a study to identify whether patients with CAT and ongoing cancer should cease or continue anticoagulation at six months may be difficult to recruit to, since such practice feels counter intuitive to clinicians. Whether such a study would be feasible regardless of scientific merit is unclear. The authors therefore propose such a study to identify the feasibility of conducting a RCT comparing six months LMWH with indefinite anticoagulation in CAT patients with ongoing malignancy.

### Research aim and objectives

The ALICAT (Anticoagulation Length in Cancer Associated Thrombosis) study was developed in response to a National Institute for Health Research (NIHR) Health Technology Assessment (HTA) commissioned call considering duration of treatment of venous thromboembolism in malignant disease (reference: 10/145), to address a specific gap in the evidence base for the management of CAT in patients with ongoing malignant disease.

The aim of this study is to examine the feasibility of conducting a phase three randomized controlled trial determining the length of anticoagulation for patients with cancer associated thrombosis.

The objectives are to: (1) Identify the practicalities of conducting a full RCT with regard to recruitment, retention and outcome measurement, specifically: the number of eligible patients that can be recruited within a one year timeframe, the dropout rate, the practical utility of measuring primary outcome measures, reporting processes, and assessment tools within the context of a full RCT. (2) Explore the logistical and attitudinal barriers to progressing to a full RCT, in particular: how and where to identify patients for recruitment, the attitudes of clinicians towards entering patients on to the ALICAT trial and prescribing anticoagulation for patients with CAT, patients’ attitudes to taking part in the trial, including individuals who consented, those who refused to participate and people who withdrew post-randomization.

## Methods/Design

### Study design

The ALICAT trial schema is summarized in Figure 1. ALICAT is a mixed-methods study involving three components: a RCT, an embedded qualitative study that will include focus groups with clinicians and interviews with patients and their relatives, and a UK wide survey exercise to map patient pathways. Each component of the study is explained below.

**Figure 1 F1:**
[figure not shown]
Trial schema.

### Randomized controlled trial

This component of the study comprises an open-label two arm RCT comparing ongoing LMWH treatment for CAT versus cessation of LMWH at six months treatment (current licensed practice) in patients with locally advanced or metastatic cancer.

#### Participant recruitment

In order to assess the feasibility of recruiting sufficient numbers of patients to inform a full phase three RCT, the ALICAT study will evaluate recruitment of patients from three different care settings within the UK: oncology outpatients, hematology outpatients, and primary care. Index VTE events shall be identified through primary and secondary care clinical databases and clinical records. In the oncology and hematology outpatient settings, potential participants will already be attending outpatient clinics for management of their cancer or CAT, and potential participants will be screened by a researcher and notified to the site principal investigator. Within the primary care setting, electronic patient records will be used to identify patients receiving treatment doses of LMWH. These records will be screened for patient eligibility of registration, by a researcher based in a primary care research institution. Patients who meet the eligibility criteria will be invited to the participating practice in order to consider participating in the study. The search will be repeated monthly in order to identify incident cases.

Potential patients will be identified when they are approaching completion of their first five months treatment with LMWH for CAT. Suitable patients will be anonymously registered. After written informed consent has been obtained, a screening baseline assessment will be conducted to ensure all the inclusion and exclusion criteria are met (see Table 1). Patients who meet the eligibility criteria will be randomized by the coordinating trials unit to either the treatment arm (continue LMWH treatment for a further six months) or the control arm (discontinue LMWH), using block randomization with varying block sizes and a 1:1 allocation ratio. Randomized patients will be asked to complete three baseline quality of life questionnaires (EORTC QLQ-C30, E5D-5 L and ESAS-r), and to keep a diary card during the six month follow up period, irrespective of the trial arm assigned.

**Table 1 T1:** Inclusion/exclusion criteria and initial assessment for the ALICAT trial

**Inclusion criteria**	1. Receiving LMWH for treatment of CAT for approximately five months
	2. Locally advanced or metastatic cancer
	3. Able to self-administer LMWH, or have LMWH administered by a carer (routine administration by a district nurse is not permissible)
	4. Able to give informed consent
	5. Age ≥16 years.
**Exclusion criteria**	1. Receiving drug other than LMWH for CAT
	2. Contraindication to continuing anticoagulation:
	a. Known allergies to LMWHs, heparin, sulfites or benzyl alcohol,
	b. Active major bleeding,
	c. History of heparin-induced thrombocytopenia,
	d. Known poor compliance with LMWH,
	3. Confirmed recurrent VTE whilst receiving anticoagulation
	4. Fitted with a prosthetic heart valve.
**Initial assessment**	1. Full blood count, urea, electrolytes, liver function, bone profile
	2. Physical examination
	3. Primary tumor and tumor treatment history
	4. Details of LMWH treatment off-trial
	5. Baseline concomitant medications
	6. Baseline comorbidities (including index VTE and bleeding event history)
	7. Use of NHS resources three months prior to commencing trial treatment.

CAT, Cancer associated thrombosis; LMWH, Low molecular weight heparin; NHS, National Health Service; VTE, Venous thromboembolism.

Information on all potentially eligible patients will be recorded, including whether or not patients were actually eligible for the trial, if they were approached about the trial, if they agreed to randomization, or were approached about taking part in a qualitative interview. Where possible, information on why the patient was not approached, randomized or approached for the qualitative interview will also be recorded.

#### Trial treatment arm

Participants randomized to the treatment arm will have already received LMWH (dalteparin (Fragmin^®^), enoxaparin (Clexane^®^), or tinzaparin (Innohep^®^)) at the treatment dose for six months. As this is a pragmatic feasibility study, participating clinicians’ treatment practices will not be altered and participants will continue with the same LMWH. LMWH will be given as a daily subcutaneous dose at the same dose and time as previously administered over the previous six months. Dosing levels will be guided by the Summary of Product Characteristics (SPC) as described in Table 2.

**Table 2 T2:** Recommended LMWH dose levels

**LMWH**	**Month one**	**Month two to six**	**Entry to ALICAT**
Dalteparin (Fragmin^®^)	200 International Units/kg total body weight, once daily	150 International Units/kg total body weight, once daily	Dose as detailed at month six
Tinzaparin (Innohep^®^)	175 International Units/kg total body weight, once daily	175 International Units/kg total body weight, once daily	Dose as detailed at month six
Enoxaparin (Clexane^®^)	150 International Units/kg total body weight, once daily	150 International Units/kg total body weight, once daily	Dose as detailed at month six

ALICAT, Anticoagulation Length with low molecular weight heparin In the treatment of Cancer Associated Thrombosis; LMWH, Low molecular weight heparin; kg, kilogram.

Switching from one ALICAT Investigational Medicinal Product (IMP) to another during the trial treatment period is allowed if deemed necessary by the treating clinician. Within current practice, the dose of LMWH may be altered at the discretion of the supervising clinician as described in Table 3. Any alteration of LMWH administration or dose and any episodes of bleeding or recurrent VTE will be documented.

**Table 3 T3:** Permissible LMWH dose alterations

**Reason for increasing dose of LMWH:**	Recurrence of symptomatic VTE despite administration of weight adjusted dose as per SPC. Some clinicians may use measurements of anti-Xa levels to guide LMWH dosing in this situation.
**Reason for decreasing dose:**	Sometimes patients may experience minor bleeding which will resolve on decreasing the dose of LMWH. This is a clinical decision of the supervising clinician that will be made based on balancing the perceived risks of recurrent VTE should LMWH be stopped or major bleeding should LMWH be continued.
**Dose for obese patients:**	Follow the SPC or local clinical practice.
**Dose for renal impairment:**	Follow the SPC. Patients with renal impairment should have dose adjustment depending on creatinine clearance/anti factor Xa levels according to local policy.

LMWH, Low molecular weight heparin; SPC, summary of product characteristics; VTE, venous thromboembolism.

#### LMWH supply

As ALICAT is a pragmatic trial, it is not the intention to change the way the LMWH is normally prescribed. A clinical trial labelling exemption has been obtained from the Medicines and Healthcare products Regulatory Authority (MHRA) and the trial will be fully exempt from the UK statutory instrument The Medicines for Human Use (Clinical Trials) Regulations 2004 No. 1031 Part 7 Regulation 46 with respect to IMP labelling and dispensing. The LMWH will be prescribed by the participant’s general practitioner (GP), oncologist or hematologist according to pre-existing local arrangements. The drug will be dispensed from commercial stock through local hospital pharmacies and community pharmacies. It is anticipated that excess treatment costs will only be incurred for participants allocated to the treatment arm at participating sites where currently it is not common practice to extend LMWH treatment for CAT beyond six months. Excess treatment costs will not be incurred for participants allocated to the control arm of the trial, irrespective of the local policy for extended LMWH treatment.

#### RCT sample size calculation

We anticipate there being at least 200 eligible patients per year in total from all three recruitment settings. We assume that not all patients who have been injecting LMWH for five months will agree to continue for a further six months. We are not sure what proportion of patients will be willing to be randomized, but we consider that at least 30% will need to agree in order to make a phase three RCT worthwhile. Therefore, the ALICAT study will aim to assess the feasibility of randomization by determining if at least 30% of potential patients will agree to randomization. We will then calculate the precision of this proportion with a 95% confidence interval. We will also estimate the proportion of patients who experience recurrent VTEs during follow up, which will inform the design of the phase three RCT.

If less than 15% of eligible patients agree to take part in the trial, a phase two RCT may not be suitable as we may not be able to recruit suitable numbers, given that a larger phase three RCT could have more stringent eligibility criteria as a result of this feasibility study. If at least 30% agree to take part, then we would consider that randomizing patients to a larger phase three trial would be feasible. Using a Fleming’s single stage design, setting p1 to 0.15 and p2 to 0.3, and with 5% significance and 90% power, then we will need to approach 62 eligible participants with details of the trial. This design requires that at least 15 out of 62 participants consent to the trial. We therefore propose a two-stage sample size. If at least 15 out of the first 62 participants recruited to the trial accept randomization, then we will continue recruitment into stage two. If fewer than 15 patients agree, we will determine at this stage that randomization within this population is not feasible.

If we expect that 200 will be the maximum potential number of eligible patients, then we can expect to be able to produce a 95% confidence interval for the percentage willing to be randomized of width 13.7% or less. For example, if the percentage is 50%, then we could expect the 95% confidence interval to be 43.15 to 56.85%. If the percentage is 30% we can expect a slightly smaller confidence interval of 23.7 to 36.3%. If only 150 patients are deemed eligible, then we can expect to calculate a 95% confidence interval for 50% randomized of 42.1 to 57.9%.

Our target registration number for this feasibility trial is therefore 200 patients, of which we hope that at least 60 patients will be randomized into the two groups. Thirty patients per arm will provide enough power to create a 95% confidence interval around the risk of VTE recurrence, which would have a width of 34% or less. As an example, if we found that the risk of VTE occurrence was 50% in the arm that stopped, we would be able to estimate a confidence interval of approximately 33% to 67% or smaller. If the risk of VTE were 8%, the confidence interval would be 0 to 19%.

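### The 15-of-62 stop rule has 87% power at a true 30% agreement rate, not the stated 90%, and no cut-off at 62 meets both stated error rates

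*Protocol article*

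**What the plan says.** The section RCT sample size calculation of the Protocol article sets out a one-sample test of willingness to be randomized.

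- Method: "Using a Fleming’s single stage design".
- Proportions: "setting p1 to 0.15 and p2 to 0.3". The first is the rate at which a trial may be unsuitable, the second the rate regarded as feasible.
- Error rates and number: "with 5% significance and 90% power, then we will need to approach 62 eligible participants with details of the trial". Sidedness is not given.
- Cut-off: "This design requires that at least 15 out of 62 participants consent to the trial".
- Consequence: "If fewer than 15 patients agree, we will determine at this stage that randomization within this population is not feasible".

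If the gate is passed, recruitment goes on towards a registration target of 200.

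**The concern.** The protocol gives its error rates together with one specific whole-number rule, at least 15 of 62. A reader will take the 5% and 90% as properties of that rule. With a count this small, each step of one in the cut-off moves power by several percentage points, so a formula that treats the cut-off as continuous can miss its target.

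Power here is the probability that the study is not abandoned when the true agreement rate is the 30% that the protocol itself calls feasible. Its complement is the risk of closing a feasible study. Feasibility of randomization is the study's central question, and this gate alone can answer it in the negative.

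**Working it through.** **Inputs.** All are from RCT sample size calculation: p0 = 0.15, p1 = 0.30 (the protocol's p1 and p2), significance 0.05, power 0.90, n = 62, cut-off r = 15. One-sided testing is an assumption; it is the reading that reproduces 62.

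**Step 1. Reproduce the plan's figures.** Fleming's formula is

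N = [(z(0.95)·√(p0(1−p0)) + z(0.90)·√(p1(1−p1))) / (p1−p0)]²

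= [(1.645·√0.1275 + 1.282·√0.21) / 0.15]² = 61.3, rounded up to 62.

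The critical value at N = 62 is N·p0 + z(0.95)·√(N·p0(1−p0)) = 9.3 + 1.645·√7.905 = 13.92. Fleming's rule rounds this and adds one: 14 + 1 = 15. Both stated figures are reproduced. Under a two-sided 5% the same formula gives 73.6, that is 74, so the protocol's 62 is a one-sided figure.

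**Step 2. Where the 90% comes from.** In the normal approximation, power at N = 62 is 90.2%, but for the fractional cut-off of 13.92. For the whole-number cut-off of 15 the same approximation gives less (mean 62 × 0.30 = 18.6, standard deviation √(62 × 0.21) = 3.61):

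- with continuity correction, P(Z ≥ (14.5 − 18.6)/3.61) = 87.2%;
- without it, P(Z ≥ (15 − 18.6)/3.61) = 84.1%.

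So the shortfall does not depend on preferring exact to approximate methods.

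**Step 3. Exact binomial properties.** Type I error is P(X ≥ r | n, 0.15) and power is P(X ≥ r | n, 0.30).

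| Approached | Cut-off | Type I error at 15% | Power at 30% | Meets both? |
|---|---|---|---|---|
| 62 | 14 | 0.0729 | 0.9245 | No, type I error too high |
| 62 | 15 | 0.0382 | 0.8735 | No, power too low |
| 62 | 16 | 0.0186 | 0.8035 | No, power too low |
| 63 | 15 | 0.0434 | 0.8888 | No, power too low |
| 64 | 15 | 0.0491 | 0.9026 | Yes |

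Cut-offs below 14 raise the type I error further, and those above 16 lower the power further. So no cut-off at 62 works, and a search over smaller numbers finds 15 of 64 to be the smallest design that meets both limits.

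**Step 4. Size.** The false-stop risk at a true 30% is 1 − 0.8735 = 12.65% against the stated 10%. That is 2.65 percentage points, or 2.65/10 = about a quarter, more.

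**Step 5. Sidedness.** If 5% were two-sided (0.025 in the upper tail), the cut-off at 62 would have to be 16, with power 80.3%. The stated power fails on either reading.

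**The case against.** The strongest reply is that nothing was miscalculated. The protocol names Fleming's design, and 62 and 15 are what that method produces. The 5% and 90% can be read as nominal inputs to a formula rather than as exact properties. This stands as a description of where the numbers came from. It does not rescue the stated power, because the rule in use is the whole-number one, and the method's own approximation gives at most 87.2% for it.

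The second reply is that the effect is small. It amounts to two approached patients. The rule of 15 of 62 reaches 90% power at a true rate of 30.8% instead of 30%, and the protocol admits that it does not know what rate to expect. The type I error is also better than stated (3.8% against 5%), and if the gate is passed the main feasibility estimate is a proportion with its confidence interval, which does not depend on the gate's power. All of this stands and bears on priority.

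A third point concerns the denominator. The same section speaks first of eligible patients approached and then of participants already recruited. The figures here assume the first reading, 62 eligible patients approached, each agreeing or not.

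**Conclusion.** The stated power is wrong as written. At least 15 of 62 has an exact type I error of 3.8% and a power of 87.3%, against the stated 5% and 90%, and no other cut-off at 62 delivers both. The chance of abandoning the study at a true 30% agreement rate is 12.7% instead of 10%. The error lies in giving a formula's nominal power to a whole-number rule, not in a miscalculated sample size.

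The conclusion assumes independent responses with a common agreement probability, a denominator of eligible patients approached, and one-sided testing; two-sided testing makes the shortfall larger. The priority is modest: the gap is 2.65 percentage points, but it sits on a binding stop rule and is almost free to correct.

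**What to change.** Make one of two changes in RCT sample size calculation:

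1. Read stage one at 64 consecutive eligible patients approached and keep the cut-off at 15 (exact type I error 4.9%, power 90.3%).
2. Keep 15 of 62 and state its exact properties: type I error 3.8% at 15%, power 87% at 30%.

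In either case, state that the test is one-sided and that the denominator is eligible patients approached. The first option adds two approached patients before the gate, within the planned 200. The second changes wording only. Neither affects eligibility, treatment or follow-up.
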